## Abstract

**Background:**

Standard of care primary treatment of carcinoma of locally advanced squamous cell head and neck cancer (LAHNSCC) consists of platinum-based concomitant chemo-irradiation. Despite progress in the treatment of LAHNSCC using modern radiotherapy techniques the outcome remains still poor. Using IMRT with SIB the escalation of total dose to the GTV is possible with the aim to improve clinical outcome. This study tests the hypothesis if radiation dose escalation to the GTV improves 2-year-LRC and -OS after concomitant chemo-irradiation.

**Methods:**

The ESCALOX trial is a prospective randomized phase III study using cisplatin chemo-irradiation and the SIB-IMRT concept in patients with LAHNSCC of the oral cavity, oropharynx or hypopharynx to escalate the total dose to the GTV up to 80.5 Gy. Chemotherapy is planned either in the 1^st^ and 5^th^ week (cisplatin 20 mg/m^2^/d d 1–5 and d 29–33) or weekly (cisplatin 40 mg/m^2^/d) during RT. RT is delivered as SIB with total doses of 80.5 Gy/70.0 Gy/56.0 Gy with 2.3 Gy/2.0 Gy and 1.6 Gy in the experimental arm and in the control arm with 70.0 Gy/56.0 Gy with 2.0 Gy and 1.6 Gy. A pre-study with dose escalation up to 77.0 Gy/70.0 Gy/56.0 Gy with 2.2 Gy/2.0 Gy and 1.6 Gy is demanded by the German federal office of radiation protection (BfS). In the translational part of the trial 100 of the randomised patients will be investigated by 18-F-FMiso-PET-CT for the presence and behaviour of tumor hypoxia twice in the week before treatment start.

**Discussion:**

The primary endpoint of the pre-study is acute radiation induced toxicity. Primary endpoint of the main trial is 2-year-LRC. By using the dose escalation up to 80.5 Gy to the GTV of the primary tumor and lymph nodes > 2 cm a LRC benefit of 15% at 2 years should be expected. The ESCALOX trial is supported by Deutsche Forschungsgemeinschaft (DFG); Grant No.: MO-363/4-1.

**Trial registration:**

ClinicalTrials.gov Identifier: NCT 01212354, EudraCT-No.: 2010-021139-15

## Background

Head and neck cancers are the seventh most frequent cancer in Germany (estimated incidence of 50/100.000 per year, Deutsche Krebsgesellschaft). The German Robert-Koch-Institut presented recently data on absolute disease numbers of all tumor entities. In 2013 for head and neck cancer there were 4.500 women and 13.000 men newly diagnosed in Germany [1]. For 2020 the new diagnosis expectations are higher: women 5.500 and men 14.300. Worldwide there are more than 550.000 new cases every year [2].

Head and neck cancers are representative for solid tumours in which new biological-imaging-based treatment strategies can be tested comparatively easily. This is true especially with regard to the impact of tumour volume, which correlates with cell number per tumour and tumor hypoxia, on response after non-surgical treatment.

Concomitant chemo-irradiation is superior to radiation alone in inoperable LAHNSCC. An absolute survival benefit of 8% at 5 years favouring chemo-irradiation was shown in the meta-analysis of the MACH-NC-group (2000) [3]. The up-date of the MACH- NC-group in 2009 included studies between 1994 and 2000. Again there was an absolute benefit of 6.5% for chemo-irradiation (independent of the setting – postoperative or primary chemo-irradiation) concerning the HR of death in comparison to local treatment alone [4]. In 2011 the MACH-NC group investigated the effect of chemo-irradiation in comparison to radiotherapy and revealed a 5-year absolute benefit (OS) due to concomitant chemotherapy for oral cavity: 8.9%, oropharynx: 8.1% and 4% for hypopharynx [5].

Besides tumor volume correlating with cell number per tumor, hypoxia is a further important biological parameter for tumor progression. Hypoxia increases radio-resistance and is a predictive factor for local failure. Hypoxia occurs in about 80% of head and neck tumors (primaries and/or lymph nodes). Based on experimental and clinical data, hypoxia is considered as a useful parameter for pre-therapeutic stratification in future randomized chemo-irradiation trials. More importantly, hypoxic sub-volumes of tumors are also evolving as target volumes for radiotherapy (“dose painting”) in some studies examining the significance of selective irradiation dose escalation. To investigate the shift of the hypoxic sub-volumes [18 F]-FMISO PET will be performed twice within 1 week before start of radiation treatment.

### Hypothesis of the trial

Over the last decade IMRT became a new standard in radiotherapy. Different trials used the advantage of IMRT concerning target volume coverage and protection of organs at risk. Analyses of acute toxicity of IMRT revealed advantage for lower toxicity compared to 3D-conformal radiotherapy with comparable treatment results.

The 2-year local control rate varies between 77–98% and the loco-regional control at 2 years between 86%–100% for non-selected tumor stages [6–8]. Two studies reported 2-year overall survival between 90–94% [9, 10] for patients with locally advanced disease.

The ESCALOX trial investigates whether dose-escalated SIB-IMRT to the primary tumor and involved cervical lymph nodes (≥2 cm) with concurrent cisplatin chemotherapy improves loco-regional control within 2 years by 15% in comparison to conventional SIB-IMRT with concurrent cisplatin.

The experimental arm of the ESCALOX-trial has not yet been tested in a multi-institutional setting. Taking into account all the mentioned results on acute and late toxicity it seems possible to apply dose escalated radiotherapy with optimization of the IMRT-plan concerning the organs at risk.

## Methods/design

### Trial organization/coordination

ESCALOX is a prospective randomized multicentre national phase III trial. The performance of the study is supported by Deutsche Forschungsgemeinschaft (DFG; MO- 363/4-1). ESCALOX is an investigator initiated trial (IIT) and is coordinated by the Department of RadioOncology and Radiotherapy of the Technical University of Munich. The Münchner Studienzentrum (MSZ) at the Technical University of Munich (Munich trial coordinating centre) is responsible for overall trial management, trial registration, database management, quality assurance including monitoring and reporting. The radio-oncological quality assurance (delineation and treatment planning) is centrally performed by the departments of radiation oncology of the two university hospitals in Munich (Technical University of Munich and Ludwigs-Maximilians-University Munich).

### Ethics, informed consent and safety

The final protocol was approved by the ethics committee of the Medical Faculty of the Technical University of Munich (2847/10 Af) and the German Federal Institute for Drugs and Medical Devices (Bundesinstitut für Arzneimittel und Medizinprodukte - BfArM; BfArM-registration number 4036421) and the German Federal Office of Radiation Protection (Bundesamt für Strahlenschutz – BfS) (BfS-registration number Z5-22463/2-2011-011).

Written informed consent is obtained from each patient in oral and written form before inclusion in the trial. Nature, scope and possible consequences of which will been explained by the responsible physician.

An independent safety board of four experts was named (three of them are radio-oncologists, one statistician). After the end of the pre-study as recommended by the German Federal Office of Radiation Protection a safety report will be sent to the BfS. During this phase there will be a stop of 6 months of the trial until the BfS gives permission for further recruitment of patients.

### Study design

The ESCALOX trial is an investigator initiated (IIT), rater-blinded, multicentre national phase III trial combining dose escalated radiotherapy of macroscopic tumor in LAHNSCC with the standard cisplatin chemotherapy (Fig. 1). The German Federal Office of Radiation Protection (BfS) demanded the enforcement of a pre-study to check the safety of a dose-escalation trial concerning the acute toxicities in a first step up to 77.0 Gy for twenty patients.

**Fig. 1 Fig1:**
[figure not shown]
ESCALOX - Trial scheme

IMRT or VMAT will be performed to apply the RT as simultaneous integrated boost. The ESCALOX trial enrols patients with LAHNSCC of the oral cavity, oropharynx or hypopharynx. Patients will be treated by the University Departments of Radiation Oncology and Radiation Therapy in Germany.

The primary endpoint of the pre-study as recommended by the German Federal Office of Radiation Protection (BfS) will be the assessment of acute toxicity. The primary endpoint of the main study is the local-regional control (LRC) at 2 years.

The secondary endpoints are disease-free survival (DFS), progression-free survival (PFS), overall survival (OS), acute and late radiation effects, adverse events, tumor hypoxia status investigated by 18-F-FMiso-PET.

### Patient selection

As defined by the German federal office of radiation protection a pre-study is performed in a step wise design. In the pre-study 20 patients will be included. The inclusion criteria are the same. For the main study a total of 250 subjects with LANHSCC are planned to recruit. For inclusion and exclusion criteria see Table 1.

**Table 1 Tab1:** Inclusion and Exclusion criteria of the ESCALOX-trial; (*) A tumour is classified as non-resectable if the probability of a complete tumor resection is estimated at a very low level (non-R0). The decision to classify a tumor as non-resectable has to be confirmed by consent of ENT-specialist, oral surgeon, radio-oncologist, radiologist and pathologist. Detailed criteria of irresectability see Adelstein et al. [55]

Inclusion criteria	Exclusion criteria
▪ Signed written informed consent ▪ Age ≥ 18 ≤ 70 years ▪ Independent of gender ▪ Independent of race ▪ ECOG 0 – 2 ▪ Tumor of oral cavity, oropharynx or hypopharynx ▪ Histology: squamous cell carcinoma, HPV-negative ▪ Curative treatment intended ▪ Tumor is classified as irresectable [11]* ▪ Woman of child-bearing age: negative pregnancy test in serum ▪ Contraception in male and female patients and their partners if of childbearing potential, willingness to use effective contraceptive method for the study duration and 2 months post therapy ▪ Sufficient bone marrow reserves during 7 days before study inclusion; (leukocytes ≥ 4 × 10^9^/l, absolute no. of neutrophiles (ANC) ≥ 2 × 10^9^/; ▪ thrombocyte count ≥ 100 × 10^9^/l; hemoglobin ≥ 10 g/dl) ▪ adaequate liver function during 7 days before study inclusion (total bilirubine ≤ 2,5 × ULN (upper limit of normal), ASAT/ALAT ≤ 2,5 × ULN, ▪ alkaline phosphatase ≤ 2,5 × ULN of the institution’s normal value) ▪ adequate kidney function during 7 days before study inclusion; serum creatinine ≤ 130 μmol/l; creatinine clearance ≥ 70 ml/min ▪ all patients should have a dental examination before starting therapy and if necessary be treated, adaptation of a teeth protection bar ▪ a percutane feeding tube should be applied before start of treatment	▪ Infiltration of the mandible and/or larynx ▪ HPV-positive proven tumors ▪ impaired renal and/or liver function ▪ secondary malignancy, unknown primary cancer, nasopharynx cancer or ▪ salivary gland cancers ▪ Metastatic disease ▪ Another cancer within 5 years of study entry ▪ Serious concomitant disease or medical condition ▪ Pregnancy or lactation ▪ Women of child-bearing potential with unclear contraception (postmenopausal ▪ women must have been amenorrheal for at least 12 months to be considered of non-childbearing potential) ▪ previous treatment with chemotherapy, radiotherapy or surgery in head and neck (except an excisional biopsy or biopsy for histology and surgery for benign disease) ▪ concurrent treatment with other experimental drugs or participation in another clinical trial with any investigational drug within 30 days prior to study screening ▪ life expectancy of < 1 year ▪ contraindications to receive Cisplatin ▪ social situations that limit compliance with study requirements

### Pathology

From the specimen taken during pan-endoscopy the tumor histology and HPV16 status will be determined.

### Imaging

During screening the standard staging program to exclude lung and liver metastasis or secondary cancer is performed by CT Thorax and ultrasound of the liver.

CT or MRI of the head and neck is performed at the time of screening and then at every follow-up visit using the RECIST-criteria version 1.1.

## Safety

### Safety pre-study

The federal office of radiation protection (BfS) requires the successful completion of a pre-study before the main study is allowed to recruit patients.

The pre-study is planned to be carried out as follows:

A pre-study was initiated before starting treatment according to ESCALOX’s planned study arms (arm A: the experimental group receiving a dose escalation up to 80.5 Gy and arm B: the control group receiving a standard dose up to 70.0 Gy).

The pre-study is analogue to the experimental group A but the dose-escalation to the macroscopic tumor and involved lymph nodes ≥ 2 cm is restricted to 2.2 Gy up to a total dose of 77.0 Gy in this SIB-volume.

In the first step 6 patients will be treated up to 77.0 Gy. After the last patient finished the RT-course there was an interval of 6 weeks defined to assess acute toxicity. When the last patient has finished the 6 weeks of follow-up and no more than 1 of the 6 patients reached grade 4 radiation induced toxicity (CTCAE v. 4.0), further 14 patients will be allowed to enter the pre-study. For all of these 20 patients the 6 weeks follow-up is fixed to assess acute toxicity as mentioned above. If no more than 2 out of all 20 patients reached grade 4 toxicity (CTCAE v. 4.0) at this time (6 weeks after end of treatment) recruitment for the main part of the ESCALOX trial with randomization into arms A and B is allowed to begin.

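### The pre-study releases 14 patients as one block and states no hold on entry to 77.0 Gy if a third counting grade 4 case has already settled the 2-of-20 limit

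*Protocol article*

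**What the plan says.** The section on patient selection fixes the size: "In the pre-study 20 patients will be included". The section on pre-study safety sets the steps.

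- Step 1: "In the first step 6 patients will be treated up to 77.0 Gy".
- Release: once the last of these has had 6 weeks of follow-up, and if "no more than 1 of the 6 patients reached grade 4 radiation induced toxicity (CTCAE v. 4.0), further 14 patients will be allowed" in.
- Assessment: "For all of these 20 patients the 6 weeks follow-up is fixed to assess acute toxicity as mentioned above".
- Final limit: the ceiling is "2 out of all 20 patients reached grade 4 toxicity (CTCAE v. 4.0) at this time (6 weeks after end of treatment"). If it is not exceeded, "recruitment for the main part of the ESCALOX trial with randomization into arms A and B is allowed to begin".

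Nothing is stated about entry between patients 7 and 20. The section on ethics, informed consent and safety says that "An independent safety board of four experts was named" but gives it no stated power to halt entry, and it places the report to the radiation protection office (BfS) after the pre-study has ended. The interim analysis plan refers back to the steps above. The section on serious adverse events takes the usual acute effects of chemo-irradiation, such as mucositis, radiodermatitis and dysphagia, out of serious-event reporting.

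**The concern.** The count against the limit can only rise as patients are added. When a third patient counts, the answer on opening the main part is fixed, and no later patient can reverse it. The rule as written has one release and one reading at the end, so patients may start the escalated dose after that point. They carry its risk without being able to change the decision that the pre-study was set up to inform.

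The exclusion from serious-event reporting adds to this. The grade 4 events most likely to count are those that the serious-event route would not bring promptly to the coordinating centre.

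**Working it through.** **Inputs from the document.** 6 then 14 patients (6 + 14 = 20); limits of 1 in 6 and 2 in 20; 35 fractions in at most 55 days; 6 weeks of follow-up. The article states no operating characteristics for the rule, so there is no figure to reproduce.

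**Assumed, because the document gives neither.** True grade 4 rate p from 2% to 40%; entry of 1, 2 or 4 patients per month.

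**Step 1: chance of passing at 6 and failing at 20 (exact binomial).**

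P(pass at 6) = (1−p)^6 + 6p(1−p)^5.

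P(pass both) = (1−p)^6 × P(at most 2 of 14) + 6p(1−p)^5 × P(at most 1 of 14).

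At p = 10%: 0.5314 + 0.3543 = 0.886, and 0.5314 × 0.8416 + 0.3543 × 0.5846 = 0.654. The difference is 0.231.

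| p | pass at 6 | pass both | pass at 6, fail at 20 |
|---|---|---|---|
| 2% | 0.994 | 0.989 | 0.006 |
| 5% | 0.967 | 0.910 | 0.058 |
| 10% | 0.886 | 0.654 | 0.231 |
| 20% | 0.655 | 0.195 | 0.460 |
| 30% | 0.420 | 0.033 | 0.387 |
| 40% | 0.233 | 0.003 | 0.230 |

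The last column is the most often that the situation can arise.

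**Step 2: patients who start after the third case is known.** Simulation with 1,000,000 runs per setting. Entry is Poisson with 4.345 weeks per month, and all 6 first-step patients are followed before the block opens. Two timings are used:

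- (a) the case is known at once, with onset uniform over weeks 3 to 13 after the start;
- (b) the case is known only at week 13, that is 7 weeks of treatment at five fractions per week (35/5) plus 6 weeks.

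Timing (b) also fits the reading in which only status at the 6-week visit counts; p is then the chance of grade 4 at that visit. Averages are over all pre-studies, including those that stop at 6 or pass.

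| p | 1/month (a), (b) | 2/month (a), (b) | 4/month (a), (b) |
|---|---|---|---|
| 2% | 0.013, 0.010 | 0.008, 0.004 | 0.003, 0.0003 |
| 5% | 0.15, 0.11 | 0.09, 0.05 | 0.03, 0.005 |
| 10% | 0.71, 0.55 | 0.46, 0.24 | 0.16, 0.03 |
| 20% | 1.96, 1.55 | 1.34, 0.75 | 0.54, 0.09 |
| 30% | 2.16, 1.77 | 1.56, 0.93 | 0.69, 0.13 |
| 40% | 1.58, 1.33 | 1.19, 0.75 | 0.58, 0.12 |

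At 2 entries per month, the chance of at least one late starter is 3% (a) or 1.5% (b) at p = 5%, 12% or 7% at 10%, and 30% or 21% at 20%.

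**Step 3: where the effect vanishes.** Under (b), if all 14 start within 13 weeks, nobody can start late and the number is zero.

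**The case against.** The strongest reply is that this is an absence in a condensed article. The safety board's remit and any ad hoc halt may be set out in the full protocol or a charter, and nothing obliges entry to continue after a third case. A reader might infer that nobody could stop the pre-study. The document does not support that; it only states no hold. What remains is that the step rule is given with its sizes, limits, timing and consequence, so how that rule works can be judged.

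Second, the 2-of-20 limit decides whether the main part opens and was not written as a stopping rule. That is correct. The hold is a safety improvement, and no statement in the plan is shown to be wrong.

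Third, the count is ambiguous. A reader might infer that any third grade 4 event during treatment already means failure. That holds only if events are counted cumulatively. The words on timing can also mean status at the 6-week visit, and then an event that has resolved by the visit would not count. Writing a cumulative count into the rule would, on that reading, tighten the BfS condition and lower the chance of passing. The fix must therefore leave the counting rule alone.

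Fourth, the true rate may be low. The discussion cites grade IV mucositis in 0–1% in a four-schedule trial without chemotherapy, and a 49-patient boost series in which dysphagia was the only grade IV acute toxicity. Neither matches 77.0 Gy with cisplatin, and another cited series pools grades III and IV, so they do not fix the rate. They do make the low rows of the tables plausible.

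Last, later patients would still add toxicity data for the BfS report. That is a real cost of a hold.

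**Conclusion.** The point holds as a modest safety gap. On either reading of the count, the stated rule lets patients start 77.0 Gy after the third counting case has settled that the main part may not open. How many do so rests on an assumed grade 4 rate, entry speed and time to recognition. At 2 entries per month the average is below half a patient at rates up to 10%, almost nil at 2%, and about one patient at 20%. Slower entry raises it; fast entry with late recognition brings it close to nil.

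A reader might infer that the main part could open wrongly or that the trial's result is biased. Neither follows: the go/no-go decision is the same with or without a hold, and the 20 pre-study patients are on top of the 250 on which the primary analysis rests.

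**What to change.** Keep both thresholds and the limit's own counting rule, and add to the pre-study section:

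- Suspend new entry to 77.0 Gy when a third patient among the 20 has radiation-induced grade 4 toxicity, pending review by the safety board and notice to the BfS.
- Resume entry if the review finds that the number of cases that count under the limit is still within it.
- During the block of 14, report grade 4 events promptly to the coordinating centre, including those exempt from serious-event reporting.

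Because entry resumes whenever the count is within the limit, the chance of passing does not change on either reading. The costs are a reporting duty, a possible short pause for a case that turns out not to count, the agreement of the BfS, and less toxicity data at 77.0 Gy after a failed pre-study.

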### Safety main study

Randomization of patients into the main part of the ESCALOX trial is only possible after successful completion of the pre-study.

For the main part of the trial there are the same conditions determined by the German federal office of radiation protection (BfS) for a step wise recruitment of patients to the experimental arm as for the pre-study. Six patients per study arm will be allowed to be treated (arm A in the SIB80.5Gy-volume up to 80.5 Gy and in arm B in the SIB70Gy-volume up to 70 Gy). “Early” follow-up for these patients is defined with 6 weeks after the end of therapy. If the last patient has finished the 6 weeks of follow-up and no more than 1 of the 6 patients in arm A (dose escalation up to 80.5 Gy) reached grade 4 radiogenic toxicity (CTCAE v. 4.0), then further 14 patients per arm will be allowed to be treated. Patient “early” follow-up will continue for at least 6 months after radiation treatment has ended.

After the end of this 6 months period all toxicities have to be reported to the BfS. Only with a new permission of the BfS further patients can be recruited and treated in the ESCALOX trial.

### Adverse event (AE)

Radiotherapy-related toxicities will be assessed using the NCI Common Toxicity Criteria (CTCAE v.4.0).

### Serious Adverse Events (SAE)

In this trial the following are not to be classified as Serious Adverse Events:Admission to hospital required by the protocolAdmission to hospital for management of the underlying diseaseDisease progression. However if, due to disease progression, a death occurs during the reporting period, it should be reported as SAE.Myelo-suppression, impaired renal function after cisplatin chemotherapy, acute side effects of radio-chemotherapy (such as fever, infection, bleeding and related hospitalizations, mucositis, radiodermatitis, dysphagia, odynophagia).

These events are expected events in the treatment of malignancies of the head and neck region. They should be reported as “Adverse Event “, but should not be reported as SAE.

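### The SAE exemption for acute chemo-radiation effects has no limit on severity or outcome, so read literally a life-threatening or fatal acute toxicity is filed only as an AE

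*Protocol article*

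**What the plan says.** The section Serious Adverse Events (SAE) opens with a categorical rule: "In this trial the following are not to be classified as Serious Adverse Events". The list that follows has these entries:

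- protocol-required hospital admissions;
- admissions to manage the underlying disease;
- disease progression;
- myelo-suppression, impaired renal function after cisplatin, and "acute side effects of radio-chemotherapy (such as fever, infection, bleeding and related hospitalizations, mucositis, radiodermatitis, dysphagia, odynophagia".

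The reason given is that such events are expected when head and neck malignancies are treated. They are to be recorded as AEs, "but should not be reported as SAE". One entry carries an exception, the one for progression: "However if, due to disease progression, a death occurs during the reporting period, it should be reported as SAE".

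Three other places bear on this:

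- **Adverse event (AE):** "Radiotherapy-related toxicities will be assessed using the NCI Common Toxicity Criteria (CTCAE v.4.0".
- **Study design (text after Fig. 1):** the pre-study's primary endpoint "will be the assessment of acute toxicity".
- **Safety pre-study and Safety main study:** recruitment proceeds in steps that depend on grade 4 events. In the pre-study the first step passes if "no more than 1 of the 6 patients reached grade 4 radiation induced toxicity", and the second reads "If no more than 2 out of all 20 patients reached grade 4 toxicity". The main study applies the same limit of 1 in 6 to the first arm A patients.

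**The concern.** Expectedness and seriousness are separate attributes of an event. The protocol uses the first to remove the second, without limit. For common, manageable effects that is a reasonable way to avoid a flood of forms. For a life-threatening bleed or a fatal infection attributed to the chemo-irradiation it is not, because those are the cases for which SAE reporting exists.

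This matters more here than in most trials. The experimental arm escalates dose, and the Discussion accepts that escalation carries a risk of more acute as well as late toxicity. Grade 4 radiation toxicity is grave enough in this protocol to decide whether recruitment may go on, yet when it is acute the SAE section treats it as non-serious. What is at stake is whether the sponsor and the safety board would see such cases as serious while patients are still being treated, above all once the stepwise checks are over.

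**Working it through.** No statistical figure is involved. The check sets the passages side by side and adds one count.

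**1. Is the exemption limited anywhere?**

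| Feature | Acute treatment effects, myelo-suppression, renal impairment | Disease progression |
|---|---|---|
| Classified as SAE | No | No |
| Upper limit by CTCAE grade | None stated | Not applicable |
| Exception if life-threatening | None stated | None stated |
| Exception if fatal | None stated | Yes, reported as SAE |
| Nature of the list | Open; the named effects are examples | Single item |

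So the text considers a fatal outcome, but for progression only. Taken literally, a death from the tumour in the reporting period is an SAE, while a fatal infection or bleed regarded as an acute treatment effect has no matching route back to SAE status.

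**2. Does another section restore it?** The AE section provides grading. The two safety sections count grade 4 events. Safety main study also requires all toxicities to be reported to the federal radiation protection office after the 6-month period. The ethics section names an independent safety board of four experts. None of these says that an exempt event becomes an SAE at some grade or outcome. The step-up rules name grade 4 and do not mention fatal events.

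**3. How many arm A patients follow the last safety step described?**

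- Inputs: 20 pre-study patients; 6 and then 14 patients per arm in the stepwise part of the main study; a safety interim analysis after the first 60 patients (Interim analysis plan); 125 per arm (Sample size calculation).
- Stepwise part: 6 + 14 = 20 per arm, so 2 × 20 = 40 randomised.
- With the pre-study: 20 + 40 = 60, which matches the 60 patients of the interim plan.
- Arm A patients remaining: 125 − 20 = 105, and 105/125 = 84%.
- The article does not say how the 60 are made up. If all 60 were randomised, 30 would be in arm A, leaving 125 − 30 = 95, and 95/125 = 76%.

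These are counts of patients exposed after the last described step. They are not estimates of missed events.

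**The case against.** The strongest reply is that the exemption changes less than it seems to. Much of that reply stands, and it rules out four stronger readings that a reader might infer.

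- **That the exemption delays or hides cases on which the recruitment steps depend.** It does not. Those steps count CTCAE grade 4 toxicity once the last patient of the step has completed 6 weeks of follow-up. The events are still recorded and graded as AEs, so they count whatever their SAE status. Nor is there a running rule that stops recruitment at a given case; the test comes at the end of each step.
- **That harm from the boost cannot show in the comparison between arms.** The secondary endpoints include acute and late radiation effects and adverse events. Exempt events remain in all of these.
- **That all toxicity of the escalated dose is exempt.** The radiation effects exempted are acute. Late mucosal ulceration, which the Discussion names as the main worry with dose-escalated boosts, is not on the list.
- **That the protocol declares fatal toxicity not to be an SAE.** It does not say so. The reading follows from an exemption without limits next to an exception written for progression deaths alone.

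A further reply is that the article condenses a fuller protocol, which may hold a general SAE definition, deadlines and recipients. That is fair for those details, and their absence is not criticised here. It does not dispose of the point, because what is printed is a stated exclusion from whatever general definition exists, and the exclusion is worded without qualification.

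Finally, grade 4 and serious are not the same thing: a grade 4 blood count may be asymptomatic. That also stands, and it argues against making every grade 4 value an SAE.

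**Conclusion.** The concern holds as a defect in a stated rule. As printed, acute chemo-radiation effects, myelo-suppression and renal impairment stay outside SAE reporting however severe they are and whatever their outcome, and only progression deaths are brought back. The rule sits badly with step-up criteria that treat grade 4 radiation toxicity as decisive.

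The practical reach is mainly the patients treated after the stepwise checks: about 105 of 125 in arm A if the 60-patient look combines the pre-study with 20 per arm, or 95 if it means randomised patients only. For them the article shows AE reporting alone for acute treatment effects of any grade. In the early cohorts the effect is confined to how quickly a grave case is recognised as serious; the decision counts themselves are unaffected.

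The conclusion rests on a literal reading of the SAE section and on no other part of the article restoring SAE status.

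**What to change.** Reconcile the Serious Adverse Events section with the two safety sections by adding a limit to the exemption, for example:

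*The exemption applies only to events that are neither fatal nor life-threatening. Any listed event, in either arm, that is fatal or life-threatening, including grade 4 radiation-induced toxicity counted in the step-up rules, is reported as an SAE and forwarded to the independent safety board. Asymptomatic haematological grade 4 values remain exempt.*

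This keeps the purpose of the exemption, since common lower-grade mucositis, dermatitis and dysphagia stay out of SAE reporting. It changes no treatment, endpoint or sample size. The cost is a short protocol change and some additional SAE forms. The article gives no basis for a firm estimate of how many. Its Discussion cites grade IV mucositis in 0–1% of patients in a four-schedule radiotherapy trial without chemotherapy, but for a different dose-escalated regimen with cisplatin the figure could be higher.
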